#### 2.2.1. Inclusion Criteria:

(1)Age ≥ 18 years old. Under Russian law, age 18 is the point at which patients transition from the pediatric to the adult population. The aim of our study is to assess the effectiveness of telemonitoring in adult patients with inflammatory bowel disease. There is no upper age limit in our study because, as long as the patient does not meet any exclusion criteria, age will not influence the study outcomes;(2)Signed informed consent;(3)Diagnosis: Crohn’s disease and ulcerative colitis (the diagnostic criteria for Crohn’s disease and ulcerative colitis are detailed in Multimedia Appendix C);

#### 2.2.2. Exclusion Criteria:

(1)Severe cognitive dysfunction;(2)Severe mental illness;(3)Oncological diseases requiring active treatment;(4)Decompensation of a comorbid condition that has worsened to the point of posing serious health risks or complicating the assessment of the trial’s outcomes;(5)Pregnant individuals;(6)Participation in other clinical studies;(7)Lack of technical skills to take part in telemedicine intervention (e.g., difficulty using a smartphone, computer, or tablet) or the absence of appropriate technology;(8)Inability to understand written Russian.

### 2.3. Consent

Every patient with IBD will receive an information brochure. A trained researcher will introduce the TIGE-Rus details to participants and discuss the trial with them. If the patient agrees to participate, they will have to sign informed consent (Multimedia Appendix D).

Patients who will be allocated to the telemonitoring group will also receive an Addendum to the informed consent containing information on health conditions requiring emergency or urgent care (Multimedia Appendix E).

### 2.4. Randomization

Randomization will be performed in 1:1 ratio between control and experimental groups using the envelope method.

### 2.5. Trial Interventions and Participant Timeline

#### 2.5.1. Stage 1

All participants will undergo a series of laboratory tests, including a complete blood count, C-reactive protein levels, and fecal calprotectin. They will also receive instrumental evaluations such as a colonoscopy with biopsy. For patients with severe IBD or jejunoileitis, a contrast-enhanced abdominal and pelvic CT scan or magnetic resonance enterography will be conducted (Table 1).

After group assignment and signing informed consent, all participants will fill out the following questionnaires:Simple Clinical Colitis Activity Index (SCCAI) [15] questionnaire for patients with ulcerative colitis/Harvey-Bradshaw index (HBI) [16] questionnaire for patients with Crohn’s disease;Short Inflammatory Bowel Disease Questionnaire (SIBDQ) [17];World Health Organization’s QoL (WHOQOL-26) [18];General Medication Adherence Scale (GMAS) [19]Patient Satisfaction Questionnaire (PSQ-18) [20];Hospital Anxiety and Depression Scale (HADS) [21];Visceral Sensitivity Index (VSI) [22];Toronto Alexithymia Scale (TAS-26) [23].

The clinical activity of the disease will be measured by Disease Activity Index (DAI) for ulcerative colitis and Crohn’s Disease Activity Index (CDAI) for Crohn’s disease [24,25].

#### 2.5.2. Stage 2

The patients in the control group will have a face-to-face consultation with a gastroenterologist, who will offer treatment recommendations, a post-discharge care plan, and dietary advice. Standard care for the control group will follow evidence-based guidelines, with outpatient visits available upon the patient’s request [24,25].

The telemonitoring group patients will receive authorized access to the personal account on the web platform. The structure of the web platform is shown on the Figure 2. It includes educational content on IBD, necessary lifestyle adjustments, and dietary guidelines, all based on international standards and resources from the Crohn’s and Colitis Foundation.

Patients will be required to log in to the web platform at least once per month. Upon logging in, they will need to provide the following information: (1) SCCAI for ulcerative colitis and the Harvey-Bradshaw index for Crohn’s disease to assess disease activity during monitoring; (2) the IBD disk questionnaire to track disease progression; and (3) results from laboratory tests (complete blood count, C-reactive protein, and fecal calprotectin). Both healthcare professionals and patients will have access to the test results. Additionally, patients can request an online consultation with a gastroenterologist via chat or phone call. They will be advised to contact a gastroenterologist if they experience disease recurrence.

Each month, gastroenterologists will call patients in the intervention group and ask questions based on a checklist (Multimedia Appendix A). They will be trained to provide immediate assistance if there are critical deviations in health indicators from the reference values (see Table 2) or complaints suggesting the onset of an acute condition.

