### 2.1. Study Design

The TIGE-Rus is designed as a prospective, parallel, two-armed, randomized controlled trial with a 1:1 allocation.

This study will consist of three stages (Figure 1).

The first stage will be a selection of patients with IBD after treatment in the Gastroenterology Department of the Sechenov University Hospital and random assignment of participants to two groups: face-to-face outpatient observation (control group) and observation using telemedicine technologies (intervention group). For every included patient, evaluation of disease activity, QoL, medication adherence, psychological well-being, and satisfaction with medical care will be performed (Figure 1).

The second stage consists of the follow-up care. For the control group, the follow-up scheme includes face-to-face appointment and follow-up recommendations on treatment, post-discharge care plan, and diet. They will be provided with the recommendations on discharge from the hospital and then on the patient’s request. The follow-up for the intervention group consists of the following: monthly completion of questionnaires on the specialized web platform by the patient; the possibility of contacting the gastroenterologist via chat or phone call on the patient’s request; and access to educational information about IBD, psychological well-being, lifestyle, diet, sexual life, pregnancy (examples in Multimedia Appendix A), posted on the web platform. In addition, patients in the intervention group will receive a monthly phone call to address any questions or concerns they may have. During these calls, they will also be interviewed using a predefined checklist (Multimedia Appendix B).

The third stage of the study will be evaluation and comparison of follow-up efficacy in the control and intervention groups. All patients will be re-hospitalized to the Gastroenterology Department after 6 months of follow-up, where the QoL, disease activity, number of IBD relapses, frequency of leukopenia in patients receiving immunomodulators, medication adherence, psychological well-being, and satisfaction with medical care will be assessed (Figure 1).

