### 2.9. Statistical Methods

The results will be analyzed only after the follow-up of all the included patients has been completed. The questionnaire scores will be calculated based on scoring guides from the questionnaire developers. Missing questions will be processed according to these guidelines. Patients without completed SIBDQ at any study point will be excluded from the analysis. Patients who refused to participate at any point in the study will be excluded from the analysis. We plan to use the full analysis set and the per protocol set (for patients without completed SIBDQ at any study point or who refused to participate at any point in the study).

Continuous variables will be tested for normality using the Shapiro–Wilk test and presented as mean (SD) or median (IQR), as appropriate. Categorical variables will be presented as percentages. For demographic and clinical data, descriptive statistics will be used to characterize the study population and to identify erroneous values. Additionally, missing values will be analyzed to determine the randomness of these omissions.

Hypothesis testing will be conducted for primary and secondary outcomes (Table 4). Quantitative variables will be compared using the Student’s T-test or the Mann–Whitney U test, as appropriate, and qualitative variables will be compared using the Fisher’s exact test. Univariate analysis of variance and multiple linear regression will be performed to analyze the association of secondary outcomes with the primary outcome. The Benjami and Hochberg (BH) false discovery rate (FDR) approach will be used to correct for multiple comparisons (*p* < 0.05). For the variables with FDR ≤ 10%, the term “showing a trend” will be used to avoid confusion with statistically significant variables.

All the analysis will be performed using a Python version of at least 3.7.0 or an R version of at least 4.2.0. A value of *p* < 0.05 will be considered statistically significant.

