Endoscopic activity of CD	Endoscopic activity of CD assessed via colonoscopy	Simple Endoscopic Score for Crohn’s Disease (SES-CD)	0–2—remission; 3–6—mild severity; 7–15—moderate severity; >15—severe;
Histological activity of IBD	Histological activity of IBD assessed via biopsy	Binary scale	No signs of inflammation in the histological material; Presence of signs of inflammation in the histological material
Laboratory tests	White blood cells concentration; Haemoglobin concentration; C-reactive protein concentration; Fecal calprotectin concentration;	Blood test and stool test	Normal values: 4–11 × 10^9^ cells/L; 120–170 g/L; 0–5 mg/L; <200 µg/g for patients with initially normal levels. <800 µg/g in both time-points for patients included in the trial with initially high levels
General medication adherence differences	Adherence to the prescribed medications, interpreted in 5 levels of adherence	GMAS score	0–10—poor adherence; 11–16—low adherence; 17–26—partial adherence; 27–29—good adherence; 30–33—high adherence;
Rate of non-scheduled medical encounters *	Unplanned visits to the Physician for IBD symptoms	As recorded in electronic health record	Number of non-scheduled visits
Rate of surgical interventions *	Surgical interventions for IBD complications	As recorded in electronic health record	Number of surgical interventions
Rate of hospitalizations *	Unplanned hospital admissions for any reason	As recorded in electronic health record	Number of unplanned hospitalizations with specification of the reason

* we assume that telemonitoring will lead to decrease in these parameters.

**Table 4 jcm-13-07734-t004:** Hypotheses proposed according to the primary and secondary study aims.

*Hypothesis*	**H_0_**	**H_a_**	
	6 months after the start of observation, there is no difference between the groups on the evaluated parameter	6 months after the start of observation, the values of the assessed parameter are higher in the telemonitoring group	6 months after the start of observation, the values of the estimated parameter are lower in the telemonitoring group
Outcomes	All primary and secondary outcomes	HRQol Generic QoL General medication adherence Satisfaction with medical care	Clinical activity of UC/CD Rate of leukopenia in patients taking immunomodulators (thiopurines, cyclosporine, tacrolimus) Depression and anxiety Visceral sensitivity Alexithymia

H_0_—null hypothesis; Ha—alternative hypothesis.

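### Baseline questionnaires, including the primary SIBDQ, come after an unblinded group assignment, so baseline scores and membership of the analysis set can depend on the arm

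*Protocol article*

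**What the plan says.** Section 2.5.1 (Stage 1) introduces the baseline instruments with "After group assignment and signing informed consent, all participants will fill out the following questionnaires". The list holds the SCCAI or HBI, SIBDQ, WHOQOL-26, GMAS, PSQ-18, HADS, VSI and TAS-26. Table 3 names the SIBDQ score as the primary outcome.

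Section 2.1 describes Stage 1 in the same order. It states random assignment first and then adds: "For every included patient, evaluation of disease activity, QoL, medication adherence, psychological well-being, and satisfaction with medical care will be performed". Table 1 puts consent and the questionnaires in a single baseline column and has no row for allocation, so it does not settle the order.

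On consent, section 2.3 says "If the patient agrees to participate, they will have to sign informed consent" and then "Patients who will be allocated to the telemonitoring group will also receive an Addendum to the informed consent". Section 2.4 follows with "Randomization will be performed in 1:1 ratio between control and experimental groups using the envelope method".

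On analysis, the null hypothesis in Table 4 is that "6 months after the start of observation, there is no difference between the groups on the evaluated parameter". Section 2.9 compares quantitative outcomes by t-test or Mann–Whitney test. It removes patients who lack a completed SIBDQ at any time point, and it adds: "Patients who refused to participate at any point in the study will be excluded from the analysis". It then names a full analysis set and a per-protocol set.

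**The concern.** A baseline measure is useful because allocation cannot have influenced it. Here the patient already knows whether to expect a web platform with monthly calls or visits on request. All the listed instruments are self-reported, and several (HADS, VSI, PSQ-18) cover anxiety or satisfaction, which pleasure or disappointment at the allocation could plausibly move. Section 3.2 itself expects telemonitoring to work partly by reducing anxiety and giving ready access to care.

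Two things are at stake. First, an imbalance in baseline scores could no longer be put down to chance, and any analysis that uses those scores would inherit the shift. Section 3.4 already expects the arms may differ in disease type, activity and severity, so a clean baseline is needed to judge comparability. Second, the first SIBDQ is collected after allocation, and a missing SIBDQ or a refusal removes the patient. Who is analysed can therefore depend on the arm.

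**Working it through.** **Sample size, for context.** Inputs from section 2.8: SD 12.52, difference 10, two-sided alpha 0.05, power 80%, loss 20%.

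- n per arm = 2 × (1.960 + 0.842)² × 12.52² / 10² = 24.6, rounded up to 25.
- Allowing for loss: 25 / 0.8 = 31.25, rounded up to 32 per arm, 64 in total.

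This reproduces the stated 64. Nothing below changes it.

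**Route 1: shifted baseline scores.** Suppose knowledge of the arm moves the baseline SIBDQ by b points between arms. The documents give no value for b; 1 to 3 points is an assumption, as is a baseline slope of 0.5.

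| Analysis | Bias | b = 1 | b = 3 |
|---|---|---|---|
| 6-month values only (as in Table 4 and section 2.9) | 0 | 0 | 0 |
| Change from baseline (not stated in the document) | b | 1 | 3 |
| Baseline-adjusted, slope 0.5 (not stated in the document) | 0.5 × b | 0.5 | 1.5 |

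Route 1 therefore does not reach the stated primary comparison. It affects the baseline tables and any analysis of the second or third kind that is added.

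**Route 2: removal after the arm is known.** Suppose a fraction q of one arm refuses, or leaves the baseline SIBDQ undone, after learning its allocation, and would have differed from those who stay by k SD at 6 months. The full-arm mean is (1 − q) × stayers + q × leavers. The mean of the stayers alone is therefore off by q × k × SD.

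| q (assumed) | k (assumed) | Bias = q × k × 12.52 |
|---|---|---|
| 0.10 | 0.25 | 0.31 points |
| 0.20 | 0.50 | 1.25 points |
| 0.20 | 1.00 | 2.50 points |

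The design difference is 10 points. With 25 analysed per arm, the standard error of the difference is 12.52 × √(2/25) = 3.54, so 1.25 points is 1.25 / 3.54 = 0.35 standard errors. The 20% matches the overall loss allowance in section 2.8, but placing it all in one arm and at the start is an assumption. The direction depends on who leaves and from which arm; equal losses of the same kind in both arms would cancel.

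**Order of consent and assignment.**

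- Section 2.5.1 names assignment before consent but only joins the two with a conjunction. Strictly, it says that both precede the questionnaires.
- Section 2.1 assigns participants after a selection step.
- Section 2.2.1 makes signed consent an inclusion criterion.
- Section 2.3 precedes section 2.4 and speaks of allocation as still to come.

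The last three read more naturally as consent first. The phrase in 2.5.1 is ambiguous and needs to be brought into line with them.

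**The case against.** The strongest reply is that the stated primary analysis compares 6-month scores without using baseline scores, so the timing of the baseline cannot bias it. For shifted scores this is correct, and the figures under Route 1 belong to analyses the article does not specify. It does not answer Route 2, because completing the baseline SIBDQ is a condition for being analysed.

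A second reply is that excluding refusers is a separate defect, and that section 2.9 also plans a full analysis set. In part this stands. Reordering would not deal with patients who withdraw later, and the exclusions may be meant for the per-protocol set only. But the exclusion sentences carry no such limit, and the parenthesis that follows does not clearly supply one. Reordering does move early refusals and undone baseline forms to before randomisation, where they cannot unbalance the arms.

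Two stronger readings are tempting. A reader might infer from section 2.5.1 that patients are assigned before they consent. That rests on word order in one phrase, and sections 2.1, 2.2.1, 2.3 and 2.4 point the other way. A reader might also conclude that the baseline is contaminated. The documents show that it could be, not that it is, and they hold no figure for how far knowledge of the arm moves any score.

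**Conclusion.** The concern holds in a limited form. By its own wording, the article collects every self-reported baseline questionnaire, the primary instrument included, after an assignment that patients can see. This weakens baseline comparability and would carry into any change-score or baseline-adjusted analysis. It does not directly bias the 6-month comparison.

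That comparison can be biased through the exclusion rules in section 2.9. The illustration gives about 0.3 to 2.5 points against the 10-point target, with 1.25 points as a middle case. These values rest entirely on assumed fractions and differences; only the SD and the target come from the document. The order of consent and assignment is an ambiguity to reconcile, not an established fault. The point deserves action because a baseline taken after allocation cannot be restored later by analysis.

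**What to change.** State one sequence in sections 2.1 and 2.5.1: informed consent; then all baseline questionnaires; then opening of the envelope; then, for the telemonitoring arm, the consent addendum and platform access. Align the wording with sections 2.2.1, 2.3 and 2.4. Record when the baseline forms were completed and when the envelope was opened, so that the order can be verified.

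In section 2.9, keep every randomised patient who has 6-month data in the main analysis, whether or not a baseline SIBDQ exists, and confine the present exclusions to the per-protocol set.

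Flag any patients already enrolled in the old order. If a change-score or baseline-adjusted analysis is reported, repeat it without them.

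The cost is a short amendment and an instruction to the one site. No visits, tests or staff are added, and the sample size stays at 64.

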##### Web Platform Description

Web platform http://ondoc.telemedai.ru/ provides access to a personal patient profile, a newsfeed with educational information (Appendix F, Figure A1), chat with the gastroenterologist (Appendix F, Figure A2), a health parameters monitoring page (Appendix F, Figure A3), information about the gastroenterologist (Appendix F, Figure A4), and the questionnaires module (Appendix F, Figure A5).

#### 2.5.3. Stage 3

After six months of monitoring, participants from both groups will be readmitted to the hospital. IBD activity will be assessed through laboratory and instrumental tests, including a complete blood count, C-reactive protein levels, fecal calprotectin, colonoscopy with biopsy, and computed tomography or MR-enterography (for patients with severe IBD or jejunoileitis). Both groups will also have to recomplete all the questionnaires to evaluate the study endpoints (see Table 1).

### 2.6. Adverse Event Reporting and Harms

An adverse event is defined as any untoward health-related occurrence in a study participant. It does not necessarily have a correlation with the allocated intervention. However, any adverse event will be recorded and reported at any study time point. Nevertheless, we developed an Addendum to the informed consent containing information on health conditions requiring emergency or urgent care for the intervention group (Multimedia Appendix D). We do not anticipate any harm related to participation in the study.

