**Figure 2 jcm-13-07734-f002:**
[figure not shown]
An online platform structure for patients in the intervention group.

**Table 1 jcm-13-07734-t001:** Summarizes the trial interventions and participant timeline.

	Study Period						
	Enrolment/Baseline 0 Weeks	Follow-Up					End of the Study (6 Months)
		1 Month	2 Months	3 Months	4 Months	5 Months	
Informed consent	X						
Eligibility criteria	X						
Demographic data	X						
Treatment in the Gastroenterology Department	X						X
Adverse events		X	X	X	X	X	X
Treatment	X	X	X	X	X	X	X
Face-to-face consultation for both groups	X						X
Observation using telemedicine technologies for the intervention group (including web-platform, phone calls)		X	X	X	X	X	
Clinical parameters							
Haemoglobin concentration	X	X	X	X	X	X	X
White blood cells concentration	X	X	X	X	X	X	X
C-reactive protein concentration	X			X			X
Fecal calprotectin concentration	X			X			X
IBD disk		X	X	X	X	X	
HBI/SCCAI questionnaire	X	X	X	X	X	X	X
Disease severity according to laboratory and instrumental data	X						X
Disease severity according to CDAI/UCDAI	X						X
Social parameters							
VSI questionnaire	X						X
TAS-26 questionnaire	X						X
HADS questionnaire	X						X
SIBDQ questionnaire	X						X
WHOQOL-26 questionnaire	X						X
Organizational parameters							
PSQ-18 questionnaire	X						X
GMAS questionnaire	X						X

**Table 2 jcm-13-07734-t002:** Limit values of the laboratory tests.

Laboratory Parameter	Critical Deviation from Reference Values
Haemoglobin concentration	Lower than 110 g/L; higher than 170 g/L
White blood cells concentration	Lower than 3 × 10^9^ cells/L; higher than 11 × 10^9^ cells/L
C-reactive protein concentration	Higher than 10 mg/L
Fecal calprotectin concentration	Higher than 200 µg/g for patients included in the trial with initially normal levels. Maintaining the level of more than 800 µg/g between two time points (Table 1) for patients included in the trial with initially high levels

**Table 3 jcm-13-07734-t003:** Study outcomes and data collection methods.

Item	Definition	Data Collection Method	Measure
Primary outcome			
Health-related quality of life (HRQol) in IBD	QoL specifically associated with bowel symptoms	SIBDQ score	Min score is 10, max score is 70. <50 means poor HRQol; >50 optimal HRQol Higher score means better outcome
Secondary outcomes			

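### Adverse events are marked monthly with no arm label, but only the telemonitoring arm has scheduled contact in months 1 to 5, so by-arm summaries of elicited events are open to detection bias

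*Protocol article*

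**What the plan says.** Section 2.6 sets a broad definition that applies to both arms: "An adverse event is defined as any untoward health-related occurrence in a study participant". It adds that "any adverse event will be recorded and reported at any study time point". In Table 1 the row "Adverse events" is marked at months 1, 2, 3, 4, 5 and at the end of study, with no arm named.

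The same table restricts the monthly contact to one arm, in the row "Observation using telemedicine technologies for the intervention group (including web-platform, phone calls", marked at months 1 to 5. The row "Face-to-face consultation for both groups" is marked only at baseline and at 6 months.

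Section 2.5.2 agrees with those two contact rows. For telemonitoring: "Each month, gastroenterologists will call patients in the intervention group and ask questions based on a checklist", and "Patients will be required to log in to the web platform at least once per month", entering symptom indices and laboratory results. For control, the arrangement between discharge and readmission is "outpatient visits available upon the patient’s request"; section 2.1 likewise describes control follow-up advice after discharge as given on request. Section 2.5.3 readmits both arms at six months.

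**The concern.** The stated schedule for adverse events and the stated follow-up do not match. A reader who takes the unlabelled row in Table 1 at face value expects monthly collection in both arms, but the article describes no scheduled monthly occasion on which a control patient could be asked.

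If the trial runs as described, one arm is prompted every month and the other mainly reports on its own initiative. The two arms' event counts would then differ partly because of how hard each was looked at. Equal true harm could appear as an excess under telemonitoring, and a true reduction could be masked. The conclusion of the article says that adverse reactions to immunomodulators will be evaluated, so a by-arm presentation of harms is likely to be read as a comparison even without a test.

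**Working it through.** The plan gives no adverse event rate and no capture probability, so there is no stated figure to reproduce. The check is a comparison of the schedule with the contacts described.

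**1. Scheduled occasions after baseline** (Table 1; sections 2.1, 2.5.2 and 2.5.3)

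| Period | Adverse event marks in Table 1 | Months with scheduled contact, telemonitoring | Months with scheduled contact, control |
|---|---|---|---|
| Months 1 to 5 | 5 | 5 (call and login) | 0 (visits on request) |
| Month 6 | 1 | 1 (readmission) | 1 (readmission) |
| Total | 6 | 5 + 1 = 6 | 0 + 1 = 1 |

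Telemonitoring has a described route for all 6 marks, control for 1 of 6.

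**2. Two readings of the row**

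- If it applies to both arms, 5 of the 6 control occasions have no described route.
- If months 1 to 5 apply to telemonitoring only, the row lacks its arm label and unequal collection is part of the design.

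Either way, Table 1 and the text have to be reconciled.

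**3. Does the monthly contact elicit adverse events?** In part. The call checklist in Appendix B asks about fever above 38 °C, unexplained loss of more than 3 kg, joint pain and blood in the stool. New occurrences of these would meet the definition in section 2.6. The checklist has no open question on other events, so the prompting is real but not comprehensive.

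**4. Direction.** Let the true event rate be the same, r, in both arms, with capture probabilities c_T (telemonitoring) and c_C (control). Then

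observed ratio = (r × c_T) / (r × c_C) = c_T / c_C.

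The true rate cancels. With c_T above c_C the ratio exceeds 1, that is, more recorded events under telemonitoring.

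**5. Illustration only.** The capture values below are assumptions, not figures from the document.

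- c_T = 0.9, c_C = 0.9: 0.9/0.9 = 1.00
- c_T = 0.9, c_C = 0.7: 0.9/0.7 = 1.29
- c_T = 0.9, c_C = 0.5: 0.9/0.5 = 1.80
- c_T = 0.9, c_C = 0.3: 0.9/0.3 = 3.00

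Given the narrow checklist, c_T could be well below 0.9; for example 0.7/0.5 = 1.40. Good questioning at month 6 would raise c_C and pull the ratio towards 1. These values show how the ratio responds to unequal capture. They do not estimate the bias in this trial.

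**The case against.** Several stronger readings are tempting, and the document does not support them.

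- **That every comparison of harms is biased.** General adverse events are not an objective, are not an outcome in Table 3 and carry no hypothesis in Table 4, so no formal test of them is stated. Unplanned hospitalisations, surgery and unscheduled visits are taken from the electronic health record, with no difference in source by arm, and depend less on a monthly call.
- **That control events in months 1 to 5 are recorded only if the patient seeks care.** Both arms are readmitted at month 6, where Table 1 also marks adverse events. Earlier control events can still be elicited then, subject to recall.
- **That leukopenia is certainly detected unequally.** Table 1 marks white cell counts monthly without an arm label. If those counts are done in both arms, detection is equal. The text describes monthly submission of results only for telemonitoring, so the question is open, not settled.
- **That a particular rate ratio is expected.** Any such figure is just the quotient of chosen capture rates.

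It can also be said that Table 1 merely omits arm labels. The IBD disk and HBI/SCCAI rows are unlabelled too, although the text describes monthly completion only for telemonitoring. That is plausible, but the telemedicine row does carry a label, so a reader may take unlabelled rows as common to both arms. If labels are missing, collection in months 1 to 5 is one-sided and the detection point remains.

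Finally, an article may leave collection procedures to the full protocol. That is fair as to absent detail. What stands is narrower: a schedule printed here that the follow-up printed here does not support. Unequal contact is also intrinsic to testing monthly telemonitoring against care on request, which is why the remedy lies in how harms are summarised and not in changing the follow-up.

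**Conclusion.** The point holds in a limited form. Table 1 and section 2.6 imply adverse event recording in both arms throughout, while scheduled contact in months 1 to 5 exists only for telemonitoring. Any by-arm summary of actively elicited adverse events is therefore open to detection bias towards more events under telemonitoring.

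The direction rests on one assumption: that monthly questioning and uploads capture more events than on-request visits plus recall at month 6. The size cannot be derived from the document. Health-record outcomes are less exposed. The primary outcome and the sample size are not touched by this point.

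**What to change.** 1. Reconcile Table 1 with sections 2.1 and 2.5.2 by showing which arm is asked about adverse events at months 1 to 5, and label the other arm-specific rows in the same way.
2. At the month-6 readmission, use one identical structured adverse event form in both arms, covering the whole six months. Base any between-arm summary on that form together with health-record events.
3. Report events found only through monthly calls or uploads separately, as monitoring data from the intervention arm.
4. State the remaining limitation with any by-arm table of adverse events.

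The cost is one form at a visit both arms already attend, plus a table correction. The downside is some recall loss over six months. That loss may be smaller in the telemonitoring arm, whose patients are prompted monthly and can see their own results, so the change reduces the bias but does not remove it.
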